**Figure 2 F2:**
[figure not shown]
Power graph for sample size calculation.

A *t*-test will be used to compare differences in ZBI variations (ZBI_followup_-ZBI_baseline_) between the two arms. A *t*-test will be also used to compare differences between the two arms in NPI, NPI-distress, olanzapine equivalents variations, as well as satisfaction questionnaires scores. Pre-specified analyses will include linear mixed effect models to compare ZBI trajectories, including arm, person's and caregiver's age, baseline MMSE, person's and caregiver's education, and olanzapine equivalents as possible predictors.

The registration data set is reported in Table 1. The CONSORT checklist (Schulz et al., 2010) for this RCT is available in the Supplementary material.

**Table 1 T1:** Registration data set.

**Data category**	**Information**
Primary registry and identifying number	ClinicalTrials.gov, NCT05977855
Date of registration	August 7^th^, 2023
Primary sponsor	University of Milano-Bicocca
Sources of monetary or material support	University of Milano-Bicocca
Contact for public or scientific queries	[name] [name] [[contact]], Fondazione IRCCS San Gerardo dei Tintori, Monza, Italy
Scientific title	Use of a diary to assess and manage Behavioral and Psychological Symptoms of Dementia [BPSDiary]
Countries of recruitment	Italy
Health condition or problem studied	Behavioral and psychological symptoms of dementia
Intervention	Diary to record five different BPSD vs. Standard of Care
Key inclusion and exclusion criteria	Inclusion criteria: - Neurodegenerative or vascular cognitive impairment (MCI or dementia) - Willingness of both caregiver and patient to take part in the study - Caregiver living with the patient, or able to cover the whole day - BPSD pertaining to the HIDA domain - Signed informed consent • Exclusion criteria: - Refusal to take part in the study
Study type	Interventional, non-pharmacological • Allocation: randomized • Masking: none • Primary purpose: treatment
Planned begin of enrollment	September 2023
Target sample size	300
Recruitment status	Recruiting
Primary outcome	ZBI variation at 3 months
Key secondary outcomes	- NPI variation - Olanzapine equivalents variation - Caregiver care-related satisfaction - NPI-distress variations^*^ - Caregiver and physician diary-related satisfaction

HIDA, Hyperactivity, impulsivity, irritability, disinhibition, aggression, agitation; NPI, Neuropsychiatric Inventory; ZBI, Zarit Burden Interview. ^*^only pertaining to items included in the diary.

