**Figure 1 F1:**
[figure not shown]
Geographical distribution of involved centers. From North to South: Castellanza (west), Monza (east), Milan, Pavia, Padua (east), Florence, Chieti, Rome, Bari.

The dyads will be randomized in a 1:1 allocation ratio with a process of covariate adaptive randomization (Suresh, 2011), using caregiver age (cut-off 60 years old; this cut-off is chosen to ensure an equal representation of young/middle-age and elderly caregivers), patient comorbidity [Cumulative Illness Rating Scale (CIRS) – comorbidity index (Salvi et al., 2008) cut-off of 1], patient gender, patient functional independence [Activities of Daily Living (ADL) and Instrumental Activities of Daily Living (IADL) preserved vs. either of them not preserved] and baseline ZBI (cut-off of 31 points). Randomization will be performed through a dedicated software, as previously shown by other groups (O'Callaghan, 2014; Guillaumes and O'Callaghan, 2019).

At baseline, the following scales will be administered to the dyads: CIRS, ADL, IADL, NPI, ZBI, MMSE. These scales will be administered in a quiet environment, free of distractions. Data will also be gathered on age, gender, education of both caregivers and patients, and drugs used by the patients.

The caregivers randomized to the intervention arm will be instructed to use the BPSDiary to register specific behaviors of interest (the BPSDiary is available in the Supplementary material). These include insomnia, agitation/anxiety, aggression (either physical or verbal), purposeless motor behavior, delusions/hallucinations. The caregiver will have to mark any occurrence of these BPSD by indicating the time of onset, ticking the appropriate severity box (mild or severe) and writing down possible triggers. An introductory page explains the definitions of each term in plain language and provides examples. The data in the diary are then transposed on an interactive excel file (available at https://drive.google.com/file/d/1i3_NY7MRg9uoe2kD5njkUhax1zS9engp/view?usp=sharing) that allows the treating physician to analyze several aspects of the BPSD of the patient, such as their temporal pattern, severity, prevalence and triggers. The BPSDiary is only offered in a “paper and pencil” version, to avoid issues related with poor digital skills of elderly caregivers in Italy.

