After the first 6 weeks the caregiver will be contacted by telephone and he/she will be asked if there are any issues related to BPSD. Caregivers randomized to the intervention arm will be asked to send the first six pages of the diary for analysis. Appropriate actions will be taken to address any issue according to the treating physician's judgment; options may include telephone counseling, scheduling a visit, prescribing or deprescribing drugs and so on. All of this will be repeated after other 6 weeks. All the approaches will be recorded and accounted for in the analyses.

The following scales will be re-administered at the end of the study (3 months): NPI, ZBI, and the satisfaction questionnaires (available in the Supplementary material). The other scales (ADL, IADL, MMSE) will not be administered, as they are judged unlikely to significantly change in the study period, and even if they do, this would probably not be related to the use of the diary.

The caregiver will be allowed to contact the treating physician at any time during the entirety of the study in case urgent actions need to be taken to address BPSD; dyads randomized to the diary will be asked to send it to the doctor for analysis. Actions taken during these unscheduled contacts will be registered in the following scheduled contact window (e.g., if the contact takes place at week 4 and quetiapine is introduced, this will be registered at the first of the two scheduled contacts at week 6).

The primary outcome will be the variation on the ZBI at 3 months. Secondary outcomes will include variation on NPI, olanzapine equivalents [calculated with the Defined Daily Doses method (Leucht et al., 2016)], caregiver care-related satisfaction, and variation on relevant NPI-distress scores at 3 months, as well as caregiver and physician diary-related satisfaction. Relevant NPI-distress scores include scores related to insomnia, agitation, aberrant motor behavior, aggression, delusions, hallucinations (i.e., the domains assessed in the BPSDiary).

The entire study will last 13 months. Enrollment will take place over the course of 9 months, and each dyad will be followed for 12 weeks. Data analysis is expected to take another month.

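### The primary t-test on ZBI change leaves out the five factors that the allocation balances, which costs efficiency and makes the test conservative to an unknown degree

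*Protocol article*

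**What the plan says.** All of this is in section 2, Methods and analysis, of the protocol article.

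- **Allocation** (after Figure 1): "The dyads will be randomized in a 1:1 allocation ratio with a process of covariate adaptive randomization". The factors are five: "using caregiver age (cut-off 60 years old"; "patient comorbidity [Cumulative Illness Rating Scale (CIRS", comorbidity index split at 1); "patient gender, patient functional independence" (ADL and IADL preserved or not); and "baseline ZBI (cut-off of 31 points").
- **Outcome:** "The primary outcome will be the variation on the ZBI at 3 months".
- **Primary test** (after Figure 2): a t-test "will be used to compare differences in ZBI variations", defined as follow-up minus baseline. No covariate is named. NPI, NPI-distress and olanzapine-equivalent changes are treated the same way.
- **Other model** (same paragraph): linear mixed models of ZBI trajectories are pre-specified. Their listed predictors are arm, both ages, baseline MMSE, both education levels and olanzapine equivalents. They are not called primary. Of the allocation factors only caregiver age is listed, although baseline ZBI may enter as one of the repeated outcomes.
- **Sample size** (before Figure 2): a 6-point difference, effect size 0.428, alpha 0.05, beta 0.05, 238 dyads, 20% drop-out, 300 in total.

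**The concern.** Subtracting baseline ZBI does not remove dependence on it. When baseline and follow-up variances are equal, dyads with high baseline scores tend to fall further, so change and baseline are negatively correlated. Two consequences follow.

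First, the change score carries variance that a baseline-adjusted model would remove. Second, the allocation deliberately balances the arms on baseline ZBI and four other factors, so the true sampling variance of the difference is smaller than under simple randomisation. The two-sample t-test does not know this: its standard error is too large whenever those factors predict change.

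At stake are power and the width of the confidence interval on the primary outcome, in a trial that already collects every covariate needed.

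**Working it through.** **1. The plan's own figure.** The implied SD is 6 / 0.428 = 14.02. With d = 0.428 and 95% power, a one-sided alpha of 0.05 gives 119 per arm, or 238, matching the article. A two-sided alpha gives 143 per arm, or 286. Sidedness is not stated. Drop-out: 238 / 0.8 = 298, taken as 300. Completers: 300 × 0.8 = 240, or 120 per arm. Two-sided power of the t-test with d = 0.428 and 120 per arm is 91.0%.

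**2. Assumptions the article does not supply.** These are the baseline to 3-month ZBI correlation r (range 0.5 to 0.8), the ratio of follow-up to baseline variance, and whether 14.02 is the SD of the change or of the score.

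**3. Formulas under equal variances (common SD s).**
- Variance of change = 2s²(1 − r)
- Residual variance of ANCOVA = s²(1 − r²)
- Ratio = (1 + r)/2
- Correlation of change with baseline = −√((1 − r)/2)

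**4. If 14.02 is the SD of change.** The effective d is 0.428 / √((1 + r)/2); power is two-sided at 120 per arm.

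| r | variance ratio | effective d | t-test | ANCOVA |
|---|---|---|---|---|
| 0.5 | 0.75 | 0.494 | 91.0% | 96.8% |
| 0.6 | 0.80 | 0.479 | 91.0% | 95.8% |
| 0.7 | 0.85 | 0.464 | 91.0% | 94.8% |
| 0.8 | 0.90 | 0.451 | 91.0% | 93.6% |

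**5. If 14.02 is the SD of the score.** The effective d is 0.428 / √(2(1 − r)) for the t-test and 0.428 / √(1 − r²) for ANCOVA.

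| r | t-test | ANCOVA |
|---|---|---|
| 0.5 | 91.0% | 96.8% |
| 0.6 | 95.8% | 98.5% |
| 0.7 | 98.9% | 99.6% |
| 0.8 | 99.9% | 100.0% |

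The gain is below 1 point from r = 0.7 upwards.

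**6. Unequal variances.** In general, the variance of change minus the ANCOVA variance is (SD_baseline − r × SD_followup)². Set the baseline SD to 1.
- Follow-up SD 1.25, r = 0.8: the difference is (1 − 1)² = 0, so there is no gain.
- Follow-up SD 1.2, r = 0.7: change variance = 1 + 1.44 − 1.68 = 0.760 and ANCOVA variance = 1.44 × 0.51 = 0.734. The ratio is 0.97, a saving of about 3%.

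**7. Type I error under covariate-adaptive allocation.** I simulated minimisation on five binary factors, with baseline ZBI split at its median, equal variances, SD of change 14.02 and two-sided 5% tests. Set A: 238 dyads, no drop-out, biased coin 0.80, 4,000 runs. Set B: 300 dyads, 20% random drop-out, biased coin 0.85, 2,000 runs. The coin probabilities are assumptions. Each cell gives the t-test, then the adjusted model.

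| r | share of change variance from the other four factors | Set A | Set B |
|---|---|---|---|
| 0.5 | 0% | 2.6% / 4.2% | 3.6% / 5.0% |
| 0.7 | 0% | 3.7% / 5.2% | 4.5% / 5.2% |
| 0.8 | 0% | 4.7% / 5.6% | 4.9% / 5.3% |
| 0.5 | 20% | 1.5% / 4.4% | 2.2% / 5.1% |
| 0.7 | 20% | 2.2% / 5.2% | 2.7% / 5.2% |
| 0.8 | 20% | 2.1% / 4.4% | 3.6% / 5.3% |

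The Monte Carlo standard error near 5% is about 0.3 points in Set A and 0.5 in Set B. In Set A, power for the 6-point difference was 90% to 95% for the t-test and 92% to 99% for the adjusted model.

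**The case against.** The sample size is computed for a t-test and the analysis is a t-test, so the plan is consistent with itself. The size of any gain rests on quantities that the article does not give. At r = 0.8 with weak other factors, the simulated type I error (4.7% and 4.9%) cannot be told from 5%. An adjusted analysis is also already planned, in the form of the mixed models. And the t-test is now published for an unmasked trial listed as recruiting, so replacing it is more than a change of wording.

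Most of this stands as a limit on size. It does not remove the point. The article itself fixes the unadjusted test for the primary comparison. The mixed models do not replace it, and they do not list CIRS, patient gender or ADL/IADL as predictors. Under equal variances, the direction of the loss is the same for every r below 1.

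Two stronger readings are tempting. A reader might infer that leaving out the allocation factors makes the primary test invalid or the estimate biased. Neither follows: arms balanced by design give an unbiased difference, and the simulated error never exceeded the nominal level for the t-test. A reader might also infer that adjustment restores the planned 95% two-sided power at no cost. The table in step 4 shows 94.8% and 93.6% at r = 0.7 and 0.8, so it does not always do so.

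**Conclusion.** The point holds as a recommended improvement in efficiency. The primary test ignores factors that the allocation was built around, and is therefore conservative by an amount that depends on how prognostic they are: from almost nothing to a true error rate of about 2% against a nominal 5%.

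The power gain at 120 per arm is 2.6 to 5.8 points (93.6 − 91.0 and 96.8 − 91.0) if 14.02 is the SD of change, variances are equal and r lies between 0.8 and 0.5. It is under 1 point at r of 0.7 or more if 14.02 is the SD of the score, and may approach zero if follow-up scores are more variable than baseline scores. I am confident of the direction and much less so of the magnitude. The gain matters most if the test is two-sided, because 238 reaches 95% power only one-sided.

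**What to change.** By a dated amendment, made before anyone compares outcomes by arm:

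- Make the primary analysis a linear model of 3-month ZBI on arm, continuous baseline ZBI, caregiver age, CIRS comorbidity index, patient gender and ADL/IADL independence.
- Report the adjusted mean difference with its 95% confidence interval.
- Keep the t-test on change as a sensitivity analysis.
- Analyse NPI, NPI-distress and olanzapine equivalents in the same way, each with its own baseline value.

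No new data are needed: all five factors are recorded before allocation, and baseline NPI and patient drugs are collected too. The cost is the amendment. The trial has no masking and is listed as recruiting, so the date and the reason for the change should be on record.

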## 2 Methods and analysis

Based on the premises mentioned above, we present here the protocol for a non-pharmacological parallel-arm randomized controlled trial named “Use of a Diary to Assess and Monitor Behavioral and Psychological Symptoms of Dementia.” The study will randomize 300 dyads (persons with dementia and their caregivers) to either the use of the BPSDiary to record BPSD or usual care. In this context, usual care means the way involved physicians usually treat their patients, according to existing guidelines, personal experience, or both. The main objective is to evaluate whether the use of the BPSDiary can lead to a significant reduction of ZBI scores at 3 months compared to usual care.

Inclusion criteria will be as follows:

- Adult patients with cognitive impairment (either MCI or dementia, either neurodegenerative or vascular or both, diagnosed by a physician with experience in dementia care)- Willingness of both caregiver and patient to take part in the study- Caregiver living with the patient, or able to cover the whole day (e.g., caregiver living in the same building)- Presence of BPSD pertaining to the HIDA domain, as inferred by the physician during the screening visit- Signed informed consent from both patient and caregiver, as requested by the ethical committee

Dyads will be excluded if they do not provide written consent to participate in the study.

The study will be conducted across the Centers for Dementia and Cognitive Decline of nine Italian centers, distributed along the peninsula. These centers have been selected based on their regional importance and expertise in managing BPSD. Sixty patients will be recruited at the Fondazione IRCCS San Gerardo dei Tintori (Monza, Lombardy), while 30 patients each will be enrolled in the remaining centers. These will include the following eight centers: Fondazione IRCCS Don Gnocchi (Milan, Italy), IRCCS Fondazione Mondino (Pavia, Italy), Ospedale Multimedica (Castellanza, Lombardy), AO Padova (Padova, Veneto), AOU Careggi (Florence, Tuscany), Sapienza University (Rome, Lazio), Ospedale SS Annunziata (Chieti, Abruzzo), Pia Fondazione Cardinale Panico (Bari, Apulia). The geographical distribution of the involved centers is shown in Figure 1.

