Sample size has been computed with the software gpower (Erdfelder et al., 2009) considering a clinically significant difference of at least 6 points at the ZBI, corresponding to an effect size of 0.428 with a *t*-test. Considering α = 0.05 and β = 0.05, 238 would be required. We hypothesized a drop-out rate of 20%, based on clinical experience on similar studies; therefore, 300 dyads are required. The power graph is shown in Figure 2.

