We acknowledge that the inclusion of people with MCI might be controversial. On one hand, MCI people are usually not expected to be cared for by a caregiver, as their level of cognitive impairment should not significantly impact their daily activities by definition. On the other hand, we cannot exclude the fact that a caregiver might be indeed present for elderly people even when their cognitive impairment is still mild, especially when there are other comorbidities. Perhaps inherently to Italian society, it is still common to provide “care” for elderly relatives even when there is no loss of autonomy. Moreover, certain behavioral abnormalities might be indeed present in the early phases of certain neurodegenerative conditions such as DLB even in the “MCI” phase. For instance, the presence of hallucinations is a core feature of the 2020 McKeith's criteria of MCI-LB (McKeith et al., 2020). In other cases, MCI might be associated with a condition called mild behavioral impairment, which may increase the likelihood of progression of the cognitive impairment (Mallo et al., 2018; Ruthirakuhan et al., 2022).

A foreseeable limitation is the relatively short period of observation. However, this is comparable with the observation period used in other tools we used to evaluate concurrent validity, such as the NPI (Kaufer et al., 1998; Pozzi et al., 2023). Moreover, the inclusion criteria imply the presence of BPSD relative to the HIDA domain, which are associated with worse outcomes in PwD. Therefore, longer periods of observation could in theory increase the drop-out rate and therefore require an even larger sample size. A period of 3 months was judged to be a good compromise between all these considerations.

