Another potential weakness is the decision to restrict BPSD assessment to only a certain subset of symptoms. Broad BPSD assessment tools that evaluate all possible disturbances already exist (Kales et al., 2017, 2018), but our intention was to target specifically those symptoms that greatly affect caregivers and result in worse outcomes for the PwD (Fauth and Gibbons, 2014; Hiyoshi-Taniguchi et al., 2018). On one hand, this will ensure that our tool is easy to use and understand, requiring caregivers to detect only the most striking behaviors, and also fast to complete, requiring only a minimum set of information to be provided. The decision to distinguish only two categories of severity (“mild” and “severe”) is in line with the perceived difficulty of caregiver to assign numbers to quantify behavior. As people of science, we tend to believe that numbers mean everything, but most of caregivers do not categorize their experiences mathematically, and forcing them to do so may result in some extent of arbitrariness that might jeopardize the assessment. We believe that our diary represents a good compromise between the two opposite tendencies of scientists and healthcare users, asking them to provide easy categories for analysis, but at the same time allowing them to reflect on and express freely their understanding of the triggers of BPSD of the PwD that they care for. While we did not conduct a proper feasibility study, during the preparation for the trial we proposed the instrument to 20 dyads at the Fondazione IRCCS San Gerardo and asked them about their opinions (qualitative data not shown). As expected, caregivers who were not cohabitating with patients reported greater difficulty in completing the diary, which led us to require cohabitation or ability to cover the whole day among inclusion criteria.

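### The primary change-score t-test can use only dyads with a 3-month ZBI (about 240 of 300) and ignores baseline ZBI and the allocation factors, while drop-out may differ by arm

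*Protocol article*

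**What the plan says.** All of this is in section 2 (Methods and analysis) of the protocol article, unless stated otherwise.

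- **Population:** "The study will randomize 300 dyads (persons with dementia and their caregivers) to either the use of the BPSDiary to record BPSD or usual care".
- **Outcome:** "The primary outcome will be the variation on the ZBI at 3 months".
- **Timing:** ZBI is taken at baseline and once more: "The following scales will be re-administered at the end of the study (3 months): NPI, ZBI, and the satisfaction questionnaires". The 6-week telephone contact lists no ZBI.
- **Primary test:** a t-test "will be used to compare differences in ZBI variations", defined as follow-up minus baseline. No covariate is named for it.
- **Drop-out:** "We hypothesized a drop-out rate of 20%, based on clinical experience on similar studies; therefore, 300 dyads are required". It is not split by arm.
- **Allocation:** covariate-adaptive, 1:1, on caregiver age, patient comorbidity, patient gender, functional independence and baseline ZBI cut at 31.
- **Other ZBI analysis:** linear mixed models of ZBI trajectories are pre-specified, with olanzapine equivalents among the predictors. They are not named as the primary test.
- **Arms:** only intervention caregivers keep the diary and send in its pages. Table 1 lists no masking.

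**The concern.** The stated test is a completer analysis by construction. Raising 238 to 300 protects its power but not its validity. A comparison of completers is unbiased if loss is unrelated to ZBI change within each arm, or if loss and its relation to change are alike in both arms. Here one arm has an extra daily task, both arms know their allocation, and the outcome is the caregiver's own burden, which is a plausible reason to leave. If the more burdened caregivers left the diary arm more often, the remaining diary dyads would look better than those randomised, and the test would favour the diary even with no effect.

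Separately, the test leaves precision unused. Baseline ZBI is collected and used for allocation, but it does not enter the test as a covariate, and neither do the other allocation factors.

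**Working it through.** **1. The plan's own figure.** Inputs: 6 points, effect size 0.428, α = 0.05, β = 0.05. Implied SD = 6 / 0.428 = 14.02.

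- One-sided: n per arm = 2 × (1.645 + 1.645)² / 0.428² = 118.2, so 119 per arm and 238 in total. This matches the article, and the exact t calculation also gives 238.
- Two-sided: 2 × (1.960 + 1.645)² / 0.428² = 141.9, so 142 per arm and 284 in total (286 by the exact t). This does not match. Sidedness is a separate matter and is not pursued here.
- Drop-out: 238 / 0.80 = 297.5, so 298; the article's 300 is consistent with this.

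**2. Dyads in the test.** 0.20 × 300 = 60 without a 3-month ZBI, leaving 240 (120 per arm) against 238 required. The stated drop-out costs no planned power: at 240 it is 95.2% one-sided and 91.0% two-sided.

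**3. Bias in closed form.** Let a fraction f of an arm be lost, and let the lost dyads have a mean change D points worse than that arm's completers. The completer mean is then too favourable by f × D. The bias in favour of the diary is f(diary) × D(diary) − f(control) × D(control).

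- Assume 20% lost per arm, D = 7 (0.5 SD) in the diary arm and D = 0 in control: 0.20 × 7 = 1.4 points, or 1.4 / 6 = 23% of the target.
- Standard error with 120 per arm: 14.02 × √(2/120) = 1.81. The shift is 1.4 / 1.81 = 0.77 standard errors, so a two-sided 5% test rejects about 12% of the time with no true effect.
- Same f and D in both arms: 0.20 × 7 − 0.20 × 7 = 0.

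**4. Simulation.** No true effect, SD 14.02, 150 randomised per arm, two-sided 5%, 10,000 trials per setting. Where loss depends on outcome, its log-odds rise by 0.5 per SD of worse change, which gives D of about 7.

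| Loss, diary / control | Where loss depends on outcome | Bias for diary (points) | False positives |
|---|---|---|---|
| 20% / 20% | diary arm only | 1.4 | 11.8% |
| 25% / 15% | diary arm only | 1.7 | 15.1% |
| 20% / 20% | diary arm only, half strength | 0.7 | 6.9% |
| 25% / 15% | both arms alike | 0.7 | 6.2% |
| 30% / 10% | both arms alike | 1.3 | 11.2% |
| 20% / 20% | both arms alike | about 0 | about 5% |

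Every loss pattern here is assumed. The article supplies only the overall 20% and, through its effect size, the SD.

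**5. What imputation under missing at random would recover.** If r is the correlation of baseline ZBI with ZBI change, imputing by arm from baseline corrects roughly the r² share of the bias and leaves 1 − r². In the first setting this leaves 1.4 points at r = 0, 1.4 × 0.91 = 1.3 at r = −0.3, and 1.4 × 0.75 = 1.05 at r = −0.5. Most of the bias remains.

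**6. What adjustment gains.** Adjusting for baseline ZBI multiplies the standard error by √(1 − r²). At r = −0.3 this is 0.954 (about 5% smaller); at r = −0.5 it is 0.866 (about 13% smaller). Both correlations are assumed.

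**The case against.** A reader might draw stronger conclusions than the article allows.

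- **That it ties drop-out to BPSD severity.** It does not. The Discussion says the inclusion criteria imply the presence of HIDA symptoms, which go with worse outcomes, and continues: "Therefore, longer periods of observation could in theory increase the drop-out rate and therefore require an even larger sample size". That concerns follow-up beyond 3 months, is hedged as theory, and does not mention severity. It partly explains why a short follow-up was chosen.
- **That caregivers in general found the diary hard.** Those who "reported greater difficulty in completing the diary" were caregivers not living with the patient, and the article answered this with an eligibility rule. Such caregivers remain eligible if they can cover the whole day, so the risk is reduced rather than removed. The remark is about completing the diary, not about leaving the trial.
- **That nothing in the plan addresses missing outcomes.** The mixed models could keep dyads with baseline data only, under missing at random, if baseline ZBI is modelled as an outcome. The article does not say that it is. The models are not the primary test, and olanzapine equivalents can change after randomisation, so adjusting for them may absorb part of the effect.
- **That dyads who stop the diary are not measured.** The article sets no such condition on the 3-month ZBI.
- **That missing imputation rules are themselves a fault.** Such rules usually sit in an analysis plan, which is not shown.

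Two further objections stand in full. The bias rests on an assumed difference between arms that no passage documents, and imputation under missing at random would not cure loss that depends on the outcome. What they leave standing is that the article fixes a primary test that can use completers only and does not adjust.

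**Conclusion.** The point holds as a weakness of a stated method, not as a demonstrated bias. The test as written uses about 240 of 300 dyads and takes no account of baseline ZBI as a covariate or of the other allocation factors. Differential loss is plausible because one arm alone has the recording task and there is no masking. Across the simulated settings the bias runs from about zero to 1.7 points in favour of the diary, against a 6-point target, with false-positive rates from 5% to about 15%. The reference case is 1.4 points and about 12%. It requires outcome-dependent loss in the diary arm and random loss in control. Planned power is not affected by the stated drop-out. The change is worth making because it is cheap and because a 3-month ZBI that is not collected may not be recoverable later.

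**What to change.** 1. Make the primary analysis an ANCOVA of 3-month ZBI on arm, baseline ZBI and the other allocation factors, with all randomised dyads as allocated. Handle missing 3-month values by multiple imputation by arm from data already collected at baseline (ZBI, NPI, MMSE, CIRS). Alternatively, use a mixed model with baseline ZBI as an outcome and without post-randomisation drug use.
2. State that the 3-month ZBI is sought from every randomised dyad, whether or not the diary is still kept. A 12-week contact is already scheduled ("All of this will be repeated after other 6 weeks").
3. Add a delta-adjusted (tipping-point) sensitivity analysis that varies the assumed outcome of drop-outs separately by arm. This addresses outcome-dependent loss directly, which step 1 alone does not.
4. Keep the completer t-test as a sensitivity analysis.

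The cost is wording in the protocol and analysis plan, a questionnaire at an existing contact for dyads who have stopped the diary, and modest analysis work. The downside is a slightly more complex primary analysis.
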